#### **6.3.3 Safety Analysis**

All subjects entered into the study at Visit 1 will be included in the safety analysis. The frequencies of AEs by type, body system, severity and relationship to study drug will be summarized. SAEs (if any) will be described in detail.

AE incidence will be summarized along with the corresponding exact binomial 95% two-sided confidence intervals.

### **6.4 Sample Size and Power**

We expect that approximately 200 subjects will be enrolled to produce 150 subjects who finish the protocol and data does not suffer motion artifacts which can cause data to be

---

omitted from group level analyses. The sample size calculation was performed using paired *t*-tests with equal variance for TYP-CI patients from both placebo therapy and OBVAT. Our published pilot data had an estimated correlation of -0.3, 0.9, -0.4, and -0.3 for CISS, NPC, PFV, beta weight from oculomotor vermis respectively. This gave a standard deviation of the difference (OBVAT- placebo/sham therapy) to be 19, 2, 19, and 27. Assuming 80% power, Alpha= 0.05, and adjusting for an 80% retention rate and 15% data loss due to motion artifacts during fMRI experiments, results in the number of subjects needed to be 37, 6, 37, 46 respectively. Using the maximum sample size for all conditions and to be satisfied, yields a cohort size of 46 per arm. We rounded the number of participants to 50 PPCS-CI for each arm.

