| Statistical And Analytic Plan   | A Wilcoxon signed test will determine whether significant changes occur between the true mean measurement after OBVAT+SCC or SCC only. A paired t -test will also be used due to its robustness property as a justifiable comparison. The direct treatment effects due to interactions between groups and time periods (before and after therapy) will be analyzed with post-hoc tests such as Tukey's method. Adjustments for multiple comparisons will be done to ensure an error rate $\alpha$ -level of 0.05.                                                                 |
| DATA AND SAFETY MONITORING PLAN | The PI will assure that the privacy of subjects, including identity and medical information, will be maintained at all times. In addition, the PI and [name] will oversee the study team and will actively monitor the study to ensure that it is carried out safely and that a subjects' symptoms do not increase sharply or over an extended period of time as a result of participation. A physician in the concussion clinic will examine any case subject that appears to show a regular increase in symptoms over the course of the study.                 |

---

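### Section 6.4 claims 80% power at an unadjusted alpha of 0.05 for each outcome, while the synopsis promises multiplicity-adjusted testing; if that adjustment reaches the sized comparison, the fMRI beta weight has less than 80% at 46–50 per arm

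*Protocol*

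**What the plan says.** Section 6.4 computes a sample size separately for CISS, NPC, PFV and the oculomotor vermis beta weight from paired t-tests. The inputs are a "standard deviation of the difference (OBVAT- placebo/sham therapy) to be 19, 2, 19, and 27" and the following: "Assuming 80% power, Alpha= 0.05, and adjusting for an 80% retention rate and 15% data loss due to motion artifacts". The text states that this "results in the number of subjects needed to be 37, 6, 37, 46 respectively". It then continues: "Using the maximum sample size for all conditions and to be satisfied, yields a cohort size of 46 per arm", and rounds up to 50. The same section also expects about 200 enrolled and 150 finishing with usable data.

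The Statistical And Analytic Plan row of the synopsis says the direct treatment effects, arising from group-by-period interactions, will be analysed with post-hoc tests such as Tukey's. It adds: "Adjustments for multiple comparisons will be done to ensure an error rate" at the 0.05 level. It names no family, number of comparisons or split.

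Sections 6.1 and 6.3.2 define one primary endpoint, a composite of NPC and PFV, to be tested by repeated measures ANOVA and a chi-squared test. fMRI is secondary there, and no adjustment is mentioned. Sections 3.1.1 and 4.2.2 restrict fMRI to the NJIT site, for which section 3.3.2 plans 50–75 subjects.

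**The concern.** The protocol fixes two things that do not meet. The sizing uses 0.05 for each outcome on its own and presents the largest N as satisfying all four. The analysis promises to hold 0.05 across multiple comparisons, which means a stricter level for any single comparison inside the family. An outcome sized to exactly 80% at 0.05 has less than 80% at a stricter level, and the beta weight is exactly that outcome because it sets the size.

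What is at stake is how a null result is read. A non-significant beta-weight comparison would be reported as coming from a test with 80% power when, depending on the family, it had noticeably less.

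**Working it through.** **Inputs (section 6.4).** Power 80%; alpha 0.05, taken as two-sided because sidedness is not stated; SD of the difference 19, 2, 19 and 27; retention 0.80; motion loss 15%; N = 37, 6, 37 and 46. No mean difference is given, so the printed Ns cannot be reproduced from first principles.

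**The plan's own figures.** The combined evaluable fraction is 0.80 × 0.85 = 0.68. Evaluable numbers of 25, 4, 25 and 31 give 25/0.68 = 36.8, 4/0.68 = 5.9, 36.8 and 31/0.68 = 45.6, which round up to the printed 37, 6, 37 and 46. At 50 per arm, 50 × 0.68 = 34 are evaluable.

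**Back-solved effect.** Paired t-test power is P[T′ > t(1 − α/2, n − 1)], where T′ is noncentral t with n − 1 df and noncentrality d√n. Setting this to 80% at α = 0.05:
- beta weight, n = 31: d = 0.520, a difference of 0.520 × 27 = 14.0
- CISS and PFV, n = 25: d = 0.584, a difference of 0.584 × 19 = 11.1

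**Tukey level.** For four cell means (2 groups × 2 periods) and 60–148 df, the critical t is 2.64–2.60, a per-comparison alpha of about 0.0105–0.0103.

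**Beta-weight power, d = 0.520:**

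| Family | Alpha | 46 per arm (31 evaluable) | 50 per arm (34 evaluable) |
|---|---|---|---|
| no adjustment | 0.05 | 80% | 84% |
| two tests | 0.025 | 70% | 75% |
| three tests | 0.0167 | 64% | 69% |
| four tests | 0.0125 | 60% | 65% |
| Tukey, four means | 0.0105 | 57% | 63% |

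**Hand check (normal approximation).** Power = Φ[(1.960 + 0.842)√(N/46) − z(1 − α/2)]. At α = 0.0125 and N = 46 this is Φ(2.802 − 2.498) = Φ(0.304) = 62%. At N = 50 it is Φ(2.921 − 2.498) = Φ(0.423) = 66%. Other evaluable fractions (0.80 and 1) and a two-sample back-solve give 60–62% and 65–66%, so the loss hardly depends on those choices. Restoring 80% at 0.0125 takes 45 evaluable, 45/0.68 = 66.2, or about 66–67 per arm.

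**Other outcomes at 46 per arm.** CISS and PFV (d = 0.584, n = 31) have 88% at 0.05, 81% at 0.025 and 72% at 0.0125. NPC is near 100%.

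**At the larger planned sample.** With 150/2 = 75 evaluable per arm, CISS and PFV have about 99% even at 0.0125. The beta weight cannot draw on that sample. The NJIT site plans 50–75 subjects, or 25 to about 37 per arm at 1:1. After the 0.68 factor that is 17–25 evaluable. With d = 0.520, power is 52–70% at 0.05 and 29–47% at 0.0125.

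**Sensitivity to the sizing formula.** Suppose the same difference of 14.0 is tested between independent arms. Using the printed correlation of −0.3, the individual SD is 27/√(2 × 1.3) = 16.7, so d = 14.0/16.7 = 0.84. With 31 per arm, power is 90% at 0.05 and 76% at 0.0125.

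**The case against.** The best reply is that the adjustment may not touch the sized comparison at all. The sentence follows one about post-hoc tests on group-by-time effects, and its natural reading is pairwise comparisons within an outcome. In a two-group, two-period design the treatment effect is the single-degree-of-freedom interaction, which the repeated measures ANOVA tests directly; it is not one of the six pairwise cell contrasts that Tukey's method governs. Moreover, section 6 has one primary endpoint, the beta weight is secondary, and a single primary endpoint needs no split of alpha across outcomes.

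Much of this stands, and it is why the loss must be stated as conditional. It does not dispose of the point. The synopsis says the treatment effects themselves will be analysed with such post-hoc tests, and nothing exempts the comparison that was sized. Calling the beta weight secondary does not help section 6.4 either, because 6.4 claims 80% for it and lets it set the size. Details of the family could properly sit in a statistical analysis plan, but here the protocol has already fixed both the sizing alpha and the promise to adjust.

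It is also fair to say that dividing the printed Ns by the attrition factor reveals nothing about alpha. The evidence for an unadjusted level is simply that 6.4 states 0.05 and mentions no adjustment. No printed figure is shown to be miscalculated.

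Finally, 150 evaluable subjects would cover any plausible adjustment for the symptom and clinical measures. That is right for those outcomes and wrong for the beta weight, which only one site supplies.

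**Conclusion.** The sizing alpha in 6.4 and the analysis alpha in the synopsis do not match, and the stated 80% for the size-setting outcome depends on a point the protocol leaves open. At 46–50 per arm, beta-weight power is 80–84% if the adjustment does not reach the sized comparison, and between 57–63% and 70–75% if it does, according to the family. This rests on a two-sided test, the paired formula as printed and an effect back-solved from the stated 80%.

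A reader might infer a flat fall to 60–65%. The documents do not support that: it requires a Bonferroni split over four outcomes, which they never mention. A reader might also infer that the section 6 primary endpoint is underpowered. The figures do not show this: taking PFV as a guide, power at 46 per arm is 88% unadjusted and 81% over two tests, and it drops below 80% only under finer splits at that size.

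For the beta weight, the single-site restriction may cost more than multiplicity does, with about 52–70% power at an unadjusted 0.05. The point is worth correcting because the printed power is a stated property of the design, but it does not undermine the trial.

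**What to change.** In section 6.4, use the alpha that the analysis will use. State which comparisons the synopsis adjustment covers, print the assumed mean difference for each outcome, and restate power for each outcome at that alpha and at the sample that will actually supply it: the full evaluable cohort for CISS, NPC and PFV, and the NJIT subset for the beta weight.

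Alternatively, test the single section 6 primary endpoint at two-sided 0.05 and place the symptom and fMRI outcomes after it in a fixed order, each at 0.05, stopping at the first non-significant result. Sizing and analysis then share one alpha, but this does not restore 80% for an outcome tested last. If PFV power stands in for the primary endpoint and the tests are independent, the chance of claiming the beta weight is 0.88 × 0.88 × 0.80 = 62% at 46 per arm and 0.91 × 0.91 × 0.84, about 69–70%, at 50. Positive correlation between outcomes raises this, but not above the beta weight's own power. The protocol should say so.

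Either route costs a wording change and a rerun of the power calculation, with no extra patients. The downside is a less favourable printed power, and under the fixed order, later outcomes that can be claimed only if the earlier ones succeed.

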## **6.5 Interim Analysis**

A trained vision therapist will monitor and administer the OBVAT to ensure that all participants complete it safely. The treating provider will determine if it is appropriate to terminate the OBVAT for any subjects that show an extended increase in symptoms.

## **7 STUDY INTERVENTION**

### **7.1 Description**

This study involves a therapeutic intervention testing the effect of OBVAT in adolescents and young adults with a PPCS-CI. Subjects will be randomly assigned to either SCC+OBVAT or SCC only arm using a random number generator. Subjects in the SCC+OBVAT arm will be asked to complete 12 one-hour biweekly OBVAT sessions in Phase 1 and an additional 4 one-hour biweekly OBVAT sessions in Phase 2. Subjects in the SCC only arm will be asked to follow SCC as instructed by their clinician for 6 weeks. Subjects will also be asked to complete at-home reinforcement during their OBVAT intervention.

All subjects will complete an optometric clinical exam, a self-reported symptom survey, fMRI and a suite of vision assessments at their study visits.

#### **7.1.1 Treatment Compliance and Adherence**

Subjects must complete all of their OBVAT sessions and assessments to receive full compensation for participation in the study. Outcome visits will not be scheduled until the subject has completed all of their OBVAT sessions, and compensation will be dispensed upon completion of each outcome visit.

---

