|                                        |                                                                                                                                                                                                                                                                                                                                                                                                                                                                                                                                                                                          |
|----------------------------------------|------------------------------------------------------------------------------------------------------------------------------------------------------------------------------------------------------------------------------------------------------------------------------------------------------------------------------------------------------------------------------------------------------------------------------------------------------------------------------------------------------------------------------------------------------------------------------------------|
|                                        | Change in vision function and fMRI measures (NJIT site only).                                                                                                                                                                                                                                                                                                                                                                                                                                                                                                                            |
| Safety Evaluations              | A trained and annually certified vision therapist will monitor all subjects during their OBVAT sessions to ensure that the sessions are being performed safely. Patient-reported symptoms will be monitored during each OBVAT session. [name] has over 45 years experience with OBVAT and will be training and certifying vision therapists. He will be available for any questions. In prior large scale randomized clinical trials studying OBVAT on neurologically normal children and young adults under [name] leadership, no adverse effects were reported. |

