## **9.7 Payment to Subjects/Families**

### **9.7.1 Payments to subject for time, effort and inconvenience (i.e. compensation)**

Subjects will be compensated for participation in the study because it requires a significant investment of time and effort. Subjects will receive up to a total of \$400 as compensation in the form of a ClinCard. Subjects will receive \$100 for completing the initial assessment, \$100 for completing outcome visit 1, and \$200 for completing outcome visit 2. For the NJIT clinical site a one year follow-up assessment will occur and additional \$200 will be given for completed outcome visit 3.

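### Payment and outcome visits both depend on finishing OBVAT sessions, with no exemption for a subject whose OBVAT is ended because symptoms increased

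*Protocol*

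**What the plan says.** Protocol section 7.1.1 contains three linked rules:

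- On payment: "Subjects must complete all of their OBVAT sessions and assessments to receive full compensation for participation in the study".
- On scheduling: "Outcome visits will not be scheduled until the subject has completed all of their OBVAT sessions".
- On timing of payment: "compensation will be dispensed upon completion of each outcome visit".

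Section 9.7.1 sets the amounts: $100 for the initial assessment, $100 for Outcome Visit 1 and $200 "for completing outcome visit 2", up to $400 in total. NJIT subjects can receive a further $200 for the one-year Outcome Visit 3. Section 9.7.1 does not mention sessions.

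Section 6.5 foresees that OBVAT may be stopped: "The treating provider will determine if it is appropriate to terminate the OBVAT for any subjects that show an extended increase in symptoms". Section 9.4.4 relies on the same possibility, together with monitoring at sessions, to support its risk-benefit judgement. The Protocol Synopsis, under Safety Evaluations, names the information collected at sessions: "Patient-reported symptoms will be monitored during each OBVAT session".

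No section says what a subject is paid, or whether that subject attends outcome visits, once OBVAT has been ended for symptoms. Section 4.3.1 is titled as an early termination visit but lists no assessments and no payment.

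**The concern.** Section 9.4.2 names a temporary worsening of concussion symptoms as the risk of OBVAT, and the protection offered is that therapy can be ended. Under section 7.1.1 the subject who triggers that protection forgoes most of the remaining money. Subjects may be as young as 11, and for them or their families the amounts are not trivial. A subject who is getting worse therefore has a financial reason to say less about it, or to carry on.

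Two things are at stake.

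- **Safety.** The safeguard works best when subjects speak freely, and the rule pulls the other way.
- **Data.** Section 6.3.2 bases the primary analysis on all randomised subjects. Section 7.1.1 gives a stopped subject neither an outcome visit nor a reason to attend one, so data after discontinuation are discouraged in those who tolerated therapy badly.

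Before Outcome Visit 1, when the randomised comparison of SCC plus OBVAT with SCC alone is made, the condition applies in arm 1 only.

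**Working it through.** **Inputs**

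- Payments (section 9.7.1): initial assessment $100, Outcome Visit 1 $100, Outcome Visit 2 $200; at NJIT also Outcome Visit 3, $200.
- Sessions due (section 4.2): arm 1 has 12 before Outcome Visit 1 and 4 more before Outcome Visit 2. Arm 2 has none before Outcome Visit 1 and 16 before Outcome Visit 2.
- Scheduling and payment rules: section 7.1.1.

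**Step 1: the protocol's own total.** 100 + 100 + 200 = $400, which agrees with section 9.7.1. With Outcome Visit 3 at NJIT, 400 + 200 = $600.

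**Step 2: reading the scheduling rule.** Outcome Visit 1 comes after 12 of 16 sessions in arm 1 and before any session in arm 2. The reference in 7.1.1 to all sessions must therefore mean those due before the visit in question.

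**Step 3: amount lost.** Loss = sum of the payments for outcome visits that can no longer be scheduled once OBVAT is ended.

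| Situation | Loss | Share of $400 | At NJIT, if Outcome Visit 3 is also lost |
|---|---|---|---|
| Arm 1, stopped before Outcome Visit 1 | 100 + 200 = $300 | 75% | 300 + 200 = $500 of $600 (83%) |
| Arm 1, stopped between Outcome Visits 1 and 2 | $200 | 50% | 200 + 200 = $400 of $600 (67%) |
| Arm 2, before Outcome Visit 1 | $0 tied to OBVAT | 0% | $0 tied to OBVAT |
| Arm 2, stopped during OBVAT | $200 | 50% | 200 + 200 = $400 of $600 (67%) |

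**Step 4: which sentence does the work.** The amounts in step 3 arise because the visits are not scheduled, so no payment falls due. If only the payment sentence were deleted, a stopped subject would still attend no outcome visit and still lose the same sums. If only the scheduling sentence were deleted, the requirement to finish all sessions for full compensation would remain, with no amount attached. Both have to go.

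**Step 5: cost of paying stopped subjects.** Cost = 300 × (arm 1 subjects stopped before Outcome Visit 1) + 200 × (arm 2 subjects stopped during OBVAT). The protocol gives no number of subjects who stop OBVAT. Section 6.4 has about 200 enrolled and 80% retention, so 200 × 0.20 = 40 lost for any reason, or 20 per arm. Taking that as an assumed number who stop but attend every visit: 20 × 300 + 20 × 200 = 6,000 + 4,000 = $10,000. With half as many it is $5,000. The extra $200 at NJIT is left out.

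**The case against.** Several counter-arguments deserve weight.

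- **Sections 7.1.1 and 9.7.1 need not contradict each other.** Both pay per visit, and 9.7.1 gives $400 as a maximum. This stands: 7.1.1 adds a condition that 9.7.1 leaves out. The problem is the condition itself.
- **Symptoms are not detected only through what subjects say at sessions.** A reader might infer that they are. However, the Synopsis has the PI monitoring symptoms and a concussion-clinic physician examining subjects with a regular increase. Section 3.1.2 keeps both arms under their treating physician, section 5.1.1 includes review of clinical notes, and section 5.3 has the therapist observing sessions. This stands. Patient report is a substantial part of the safeguard, not all of it.
- **Reporting a symptom forfeits nothing by itself.** Ending OBVAT requires a sustained or marked increase and, in section 6.5, a provider's judgement. This is true, but a subject who knows that stopping costs money still has reason to understate what leads to it.
- **The protocol never says that a subject stopped for safety is refused payment.** This is true, and the consent pages are not in the text reviewed. But 7.1.1 is worded as a general rule with no exemption, so forfeiture is its literal effect.
- **Arm 2 can lose money too.** Withdrawal for safety under section 4.3 is possible in either arm. That is so, but before Outcome Visit 1 arm 2 has no session condition.

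A reader might also infer that the one-sided incentive biases the comparison of symptoms and adverse events in favour of OBVAT. The document does not support this. Section 6.3.3 states no comparison of adverse events between arms. Arm 1 has up to 12 monitored sessions before Outcome Visit 1 and arm 2 has none, which would push towards more recorded symptoms in arm 1. The endpoint in section 6.1 rests on NPC and PFV, assessed by optometrists who are to be blinded (3.2, 9.1.2). Symptom surveys are completed at the outcome visits, where payment does not depend on the score.

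**Conclusion.** The point holds as a defect in the payment and scheduling rule. Taken literally, 7.1.1 costs a subject whose OBVAT is ended for symptoms $300 of $400 in arm 1 before Outcome Visit 1, and $200 of $400 in arm 1 after that visit or in arm 2 during OBVAT. At NJIT $200 is added if Outcome Visit 3 is lost as well. Before Outcome Visit 1 the condition applies in arm 1 alone.

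The consequences are a financial disincentive to report worsening or to stop, and no route to an outcome visit for stopped subjects who belong in the intention-to-treat analysis. The disincentive is inferred from the payment structure; the protocol offers no evidence on how subjects would respond. The size and net direction of any resulting bias between arms cannot be established, so the case rests on the safeguard, on completeness of follow-up, and on how little the correction costs.

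**What to change.** In section 7.1.1, delete both the session condition for full compensation and the sentence that withholds outcome visits until sessions are finished. State instead that subjects whose OBVAT was stopped are still invited to the outcome visits, and that each assessment attended is paid at the section 9.7.1 amount whatever the number of sessions completed. Tell subjects this at consent. The criteria for ending OBVAT are not touched.

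The cost is a small change to the protocol and consent wording, a weaker incentive to finish sessions, and the payments to stopped subjects who attend: about $10,000 under the assumption of 20 per arm. These sums are already provided for subjects who complete.

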### Study Interventions and Measures:

This study will compare the outcomes of adolescents and young adults with persistent post-concussive symptoms with convergence insufficiency who are randomized to standard-community concussion care (SCC) plus office-based vergence/accommodative therapy (OBVAT) versus those randomized to SCC alone to evaluate the effect of OBVAT in adolescents and young adults with PPCS-CI.

The primary endpoint of this study is the reduction in visual symptoms. This study will also assess the change in vision function measures and fMRI results of those that perform OBVAT compared to those who complete SCC. Additionally, this study will also assess the dose response of 12 OBVAT sessions as compared to 16 sessions.

---

---

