| Study Phases
Screening
Study Treatment
Follow-Up | 
Screening and Initial Assessment: All patients who present to the Children’s Hospital of Philadelphia, Somerset Pediatric Group, JFK Institute or Rothman Orthopedic with a concussion date of injury 1-6 months ago will be screened for enrollment as case subjects using the protocol inclusion and exclusion criteria. Clinicians specializing in concussion management will identify potential subjects under their care in clinics after a standard clinical evaluation that consists of a detailed history and examination. A member of the study team will introduce the study to subjects deemed eligible to participate, obtain verbal consent to screening, and screen them against study inclusion and exclusion criteria. Eligible subjects will have time to ask questions and consider participation prior to consenting. Parental/guardian permission (informed consent) and, if applicable, child assent, will be obtained prior to any study related procedures being performed. After consenting to participate, subjects will complete an initial optometric exam, vision assessments, fMRI (NJIT site only), and a patient-reported symptom questionnaire. Data from control subjects recruited from local colleges and universities who did not have a recent concussion have already been collected.
 
Intervention: Case subjects will be randomly assigned into one of two arms. Arm 1 will begin OBVAT immediately, while arm 2 will start with 6 weeks of SCC followed by the OBVAT intervention. A member of the study team will connect subjects with the study vision therapist who will perform their OBVAT sessions. Arm 1 subjects will complete 12 1-hour bi-weekly OBVAT sessions with the vision therapist in addition to SCC while arm 2 subjects complete SCC alone. After 6 weeks, subjects will complete outcome visit 1. After outcome visit 1, arm 1 cases will complete 4 more OBVAT sessions and then complete outcome visit 2. After the initial 6 weeks, arm 2 cases will complete 16 1-hour bi-weekly OBVAT sessions and then complete outcome visit 2. All case subjects will complete at-home reinforcement activities during their OBVAT intervention.
 |

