### **3.3 Study Duration, Enrollment and Number of Sites**

#### **3.3.1 Duration of Subject Study Participation**

The study duration per subject will be up to 11 weeks  $\pm$  3 weeks for arm 1 and 17 weeks  $\pm$  3 weeks for arm 2. With up to 7 days screening, 6 weeks  $\pm$  2 weeks Phase 1, and up to 8 weeks  $\pm$  2 weeks Phase 2 for arm 2 and 2 weeks  $\pm$  1 week for Phase 2 arm 1.

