### **4.2 Study Treatment Phase**

All subjects who are deemed eligible and interested in participating in the study after the screening will complete a written or electronic informed consent at their screening visit, before any study procedures take place. Subjects will then complete an initial assessment prior to the start of the treatment phase. The initial assessment may take place on the same day as the screening visit after informed consent has taken place.

For arm 1, the study treatment phase will consist of 12 one-hour OBVAT sessions bi-weekly followed by Outcome Visit 1. After completion of Outcome Visit 1, arm 1 subjects will complete 4 additional one-hour OBVAT sessions bi-weekly followed by Outcome Visit 2.

For arm 2, subjects will complete 6 weeks of SCC followed by Outcome Visit 1. After completion of Outcome Visit 1, arm 2 subjects will complete 16 one-hour sessions of OBVAT bi-weekly followed by Outcome Visit 2.

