## **5.2 Efficacy Evaluations**

### **5.2.1 Diagnostic Tests, Scales, Measures, etc.**

Subjects will complete an optometric examination, vision assessments, fMRI (NJIT clinical site only) and symptom report at all assessment visits (except arm 1 will not perform an fMRI at the second outcome). Data obtained from these assessments will be tracked and compared between the start and end of the treatment phase for all case subjects enrolled in the study, regardless of treatment arm.

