#### **6.3.2 Efficacy Analysis**

The primary analysis will be based on an intention to treat approach and will include all subjects randomized at their initial assessment.

The primary efficacy endpoint will be the change in composite clinical parameters of near point of convergence and positive fusional vergence between the initial assessment and the outcome visits. A repeated measures ANOVA will be used to assess the clinical parameters as well as the chi-squared test using predetermined published optometric benchmarks for improvement.

Secondary endpoints will include the rate of symptom remediation in OBVAT+SCC group compared to SCC alone, change in vision function, and fMRI measures between the start and end of the treatment phase.

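### Outcome visits wait on completed OBVAT sessions, with no exception for subjects stopped for worsening symptoms, so Outcome Visit 1 can be lost in arm 1 only

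*Protocol*

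**What the plan says.** - **Scheduling rule.** Section 7.1.1: "Outcome visits will not be scheduled until the subject has completed all of their OBVAT sessions". No exception is given.
- **Stopping rule.** Section 6.5 has the treating provider decide whether to "terminate the OBVAT for any subjects that show an extended increase in symptoms". Section 9.4.4 also allows early termination for a sharp or prolonged rise in symptoms. Neither says which assessments follow. Section 4.3.1 is headed as an early termination visit but describes none.
- **Timing of Outcome Visit 1.** Synopsis, Study Phases: "After 6 weeks, subjects will complete outcome visit 1". Section 3.3.1 sets the phase lengths ("With up to 7 days screening, 6 weeks" ± 2 weeks for Phase 1).
- **What each arm receives before that visit.** Under 4.2, arm 1 has 12 OBVAT sessions. For the other arm: "For arm 2, subjects will complete 6 weeks of SCC followed by Outcome Visit 1".
- **Who is compared.** Section 5.2.1 compares assessment data "for all case subjects enrolled in the study, regardless of treatment arm". The primary analysis in 6.3.2 is by intention to treat and "will include all subjects randomized at their initial assessment".
- **Endpoints.** The abstract states: "The primary endpoint of this study is the reduction in visual symptoms". Section 6.1 instead makes the composite of near point of convergence (NPC) and positive fusional vergence (PFV) primary, and 6.2 lists symptom remediation as secondary.

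**The concern.** A subject whose OBVAT has been ended can never meet the 7.1.1 condition. The timing rules require that subject's Outcome Visit 1 at about 6 weeks, while 7.1.1 tells the site not to schedule it. Three clinical sites have to apply these rules and could resolve the conflict differently.

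Outcome Visit 1 is the only visit at which OBVAT plus SCC is compared with SCC alone, since arm 2 starts OBVAT afterwards. The reason for stopping is a rise in symptoms, and symptom reduction is an endpoint. Arm 1 could therefore lose subjects who did badly on symptoms while comparable arm 2 subjects are still measured. An analysis plan can specify how missing data are handled, but for visits never held it can offer only assumptions.

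**Working it through.** **1. Which sessions does the rule mean?** Read literally, all sessions means 16 in each arm, and Outcome Visit 1 could not be held at 6 weeks in either arm. Section 4.2 places that visit after 12 of 16 sessions in arm 1 and before any in arm 2, so the workable reading is the sessions due before the visit. The rest uses that reading.

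**2. Does it fit the 6-week schedule?** Weeks to finish = 12 / sessions per week.

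| Sessions per week | Week of 12th session | Window (6 ± 2 weeks) |
|---|---|---|
| 2 | 12/2 = 6 | on time |
| 1.5 | 12/1.5 = 8 | at the edge |
| 1 | 12/1 = 12 | outside |
| stopped early | never | no visit |

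The rules agree for an adherent subject. They conflict for arm 1 subjects who fall well behind or are stopped.

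**3. Which arm?** Before Outcome Visit 1 only arm 1 has OBVAT sessions to complete, so this rule can bar only arm 1 subjects from that visit.

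**4. Possible size.** The protocol gives no stopping rate. Assumed, not from the protocol:

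- a share p of subjects (2% to 10%) scores d within-group SD worse (1 to 1.5) on symptoms;
- the same subgroup exists in both arms and there is no true effect;
- in arm 1 these subjects are stopped and unmeasured, while arm 2 is fully measured;
- the symptoms that trigger a stop track the CISS;
- the arms are compared by a pooled two-sample t-test on observed data, two-sided 0.05.

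Arm sizes are 75 (half of the 150 evaluable subjects) and the 50 of section 6.4.

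False benefit in whole-arm SD = p·d / √(1 + p(1−p)d²):

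- p = 0.02, d = 1: 0.02/√1.0196 = 0.020
- p = 0.05, d = 1.5: 0.075/√1.1069 = 0.071
- p = 0.10, d = 1.5: 0.15/√1.2025 = 0.137

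CISS SD from 6.4 (SD of the difference 19, correlation −0.3, equal variances): 19/√(2 × 1.3) = 11.8 points.

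Difference detectable with 80% power at 75 per arm: (1.960 + 0.842) × √(2/75) = 0.46 SD.

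Type I error comes from simulation, 40,000 runs per case:

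| p, d | False benefit (SD) | CISS points | Share of 0.46 SD | Type I error, 75 per arm | Type I error, 50 per arm |
|---|---|---|---|---|---|
| 2%, 1 | 0.020 | 0.2 | 4% | 5.1% | 5.0% |
| 5%, 1 | 0.049 | 0.6 | 11% | 5.9% | 5.7% |
| 5%, 1.5 | 0.071 | 0.8 | 15% | 7.2% | 6.6% |
| 10%, 1 | 0.096 | 1.1 | 21% | 8.7% | 7.5% |
| 10%, 1.5 | 0.137 | 1.6 | 30% | 13.0% | 10.3% |

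As a cross-check, a normal approximation at 50 per arm with a 1 SD gap gives 5.7% for 5% stopped and 7.8% for 10%, close to the simulated 5.7% and 7.5%.

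**The case against.** The strongest reply is that 7.1.1 is a compliance rule. Its heading is about adherence, and its sentences link sessions and visits to compensation. Section 6.5 ends the OBVAT, not study participation, and 4.2.5 and 4.2.8 list the outcome assessments without a session condition. A site could reasonably decide that a stopped subject has no sessions outstanding and hold the visit. That reading is available, but the sentence governs scheduling and is unqualified, so sites are not bound to it.

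Several limits stand:

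- For adherent subjects there is no conflict with the schedule.
- The synopsis reports no adverse effects in earlier OBVAT trials (in neurologically normal subjects), and 9.4.2 expects any exacerbation to resolve within hours. Both point to a low stopping rate, at which the bias is negligible.
- The calculation is one-sided by construction. Under 4.3 the investigator may withdraw subjects of either arm for safety, which could also remove some arm 2 subjects. The protocol does not name a plain observed-data t-test for symptoms.
- A missed visit creates missing data; it does not formally take the subject out of the intention-to-treat set. The conflict with 6.3.2 is practical: the subject is to be analysed, but no outcome is collected.

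**Conclusion.** The point holds, and the text is wrong as written. Section 7.1.1 and the time-based schedule give opposite instructions for a subject whose OBVAT is ended before Outcome Visit 1. Following 7.1.1 loses that visit in arm 1 only, for a reason linked to a symptom endpoint. This textual conflict depends on no assumed figure.

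The size is uncertain. Under the assumptions above it runs from negligible (2% stopped, 1 SD worse) to a type I error of 13.0% with 75 per arm (10% stopped, 1.5 SD worse). The bias disappears if nobody is stopped or if sites do not apply 7.1.1 to stopped subjects. The direction applies to symptoms, primary in the abstract but secondary in 6.2. No effect on the NPC/PFV composite of 6.1 has been shown.

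Section 4.3.1 raises a separate issue: it discards all longitudinal data of subjects who choose to withdraw, which plainly contradicts 6.3.2. It is not part of the figures above. The change should be made; confidence in its practical importance is moderate.

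**What to change.** - In 6.5 and 7.1.1, state that a subject whose OBVAT is ended early stays in the study and, unless consent is withdrawn, attends Outcome Visits 1 and 2 at the planned weeks.
- In 7.1.1, limit the scheduling condition to subjects still receiving OBVAT, and hold it within the 3.3.1 window (6 weeks ± 2 for Outcome Visit 1), so that a subject who is behind on sessions is still assessed on time.
- In 4.3.1, keep data collected before withdrawal in the analysis, to agree with 6.3.2.

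The cost is protocol wording, site training and some follow-up of subjects off treatment, at visits already planned and compensated. No extra subjects are needed.
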